**Methods:**

IMPROVE is a cluster-randomized controlled trial with two arms to evaluate and compare the effects of two different bundles of implementation strategies on intervention fidelity expressed as adherence and responsiveness at 12 and 24 months (primary outcomes). Thirty schools in two municipalities will participate in the study reaching about 1400 families per school year. In stakeholder workshops, key implementation determinants were identified according to the domains of the Consolidated Framework for Implementation Research. Through a consensus process with stakeholders, two bundles of implementation strategies were tailored to address context-specific determinants. Schools randomly assigned to group 1 will receive bundle 1 (Basic) and group 2 will receive bundle 1 + 2 (Enhanced). Bundle 2 consists of external facilitation, fidelity monitoring and feedback strategies. Secondary outcomes will include change in acceptability, appropriateness, feasibility, and organisational readiness as perceived by school staff. In addition, child weight status and diet, and parents’ feeding practices and risk of type 2 diabetes will be monitored. Linear and ordinal regression analysis will be used to test the effect on the primary and secondary outcomes, taking clustering and covariates into consideration where needed. Process evaluation will be conducted through key stakeholder interviews to investigate experiences of the program and perceptions on sustainability.

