The program has been evaluated in schools with mixed socioeconomy [33] and in disadvantaged areas [34] in the greater Stockholm area. Fidelity to the intervention components was high for the MI component performed by external MI counsellors in the first two trials, and the classroom component performed by teachers. In the first trial [33] we found significant beneficial effects on dietary habits (higher consumption of fruit and vegetables and lower consumption of unhealthy foods and drinks in the intervention group relative to control). In the second trial [34] we also found a significantly lower BMI z-score in children with obesity at baseline compared to control. In an attempt to increase the involvement of parents in the program, a validated short non-invasive tool to identify individuals at high risk for type 2 diabetes (FINDRISC) [35] was added to the third trial. Undiagnosed diabetes and prediabetes are common in Sweden [36]. If detected early, lifestyle modification can reverse this condition [37] and potentially have beneficial effects on the whole family. In addition, an increased emphasis was placed on parental feeding practices and child physical activity, and the MI was conducted by trained school nurses in the third trial [29]. Results from the third trial running from 2017 to 2019 are in line with the previous studies (manuscript submitted).

During previous evaluations of the HSS program the following implementation barriers were encountered: low priority given to health promotion in schools relative to achievement of learning outcomes [38], lack of positive leadership [39], lack of preparation time [40], the need for clear communication and collaboration between teachers and parents, especially regarding the children’s home assignments [41], and difficulty to engage parents in low-income areas due to stressful everyday life and lack of knowledge and parenting skills [16, 39]. Furthermore, it was found that commitment among staff is important for high intervention fidelity [38]. Addressing these barriers could be achieved through the establishment of an implementation team [38], and by receiving resources and support from external partners such as public health teams [42, 43]. Ultimately, there are numerous barriers that impact the successful implementation of school-based health programs like the HSS that warrant tailored approaches that target these determinants to achieve high fidelity.

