### Data management and statistical analysis

Data collection will be performed in a secure web platform Research Electronic Data Capture (REDCap) for building and managing online databases and surveys [67, 68]. All data will be stored electronically in password-protected folders on a secure data server with systematic back-up routines at Karolinska Institutet to avoid unauthorized access. Folders containing raw data will be stored separately from the data being used in the analysis. Access to data will be restricted to the research personnel working directly with data entry or analyses. A detailed statistical analysis plan will be developed in collaboration with an academic statistician prior to the start of data analysis.

Baseline characteristics at both school and individual level will be cross-tabulated for group 1 and 2 to check for balance and to provide an overview of the study population. Continuous and normally distributed variables will be represented as mean, standard deviation and range. Non-normally distributed variables will be represented as median and interquartile ranges, and categorical variables will be presented as frequencies and percentages in each category.

Assessment of the primary outcomes adherence score and responsiveness score after 12 and 24 months will be performed on the individual level. Between-group effects in the adherence score (0–4) will be analyzed using ordinal logistic regression. Between-group effects in the responsiveness score (4-20) will be analyzed using mixed linear regression. The following factors will be explored as potential moderators of fidelity to intervention: school size, fidelity to implementation strategies, baseline organisational readiness, parent educational level and country of birth.

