### Sample size and power calculation

Power based on the primary outcome “adherence score” was calculated for the sample size of 400 consenting parents in each group. Assuming that the difference in the log odds of the groups will be 0.3, 0.4 or 0.5 (maximum score 4), this corresponds to odds ratios of 1.35, 1.5 and 1.65, respectively. The power was simulated with 5000 replications and found to be 0.44, 0.66, and 0.86 for the three different scenarios. Power for the primary outcome “responsiveness score” was calculated for the same sample size as above, using the mean differences of 0.8, 1.6 and 3.2 (maximum score 20). The standard deviation was assumed to be 4, 8 and 16 for each option. With an SD of 8, the power for the three scenarios is 0.29, 0.81 and 0.99 respectively for this outcome.

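### Prognostic baseline variables already being collected are given an exploratory moderator role, and primary adjustment is left to where needed; a short fixed covariate set would be a nearly free gain of uncertain size

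*Protocol article*

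**What the plan says.** Under Data management and statistical analysis, the Protocol article assigns ordinal logistic regression to the adherence score (0 to 4) and mixed linear regression to the responsiveness score (4 to 20). No covariate is named for either. The same paragraph then lists factors that "will be explored as potential moderators of fidelity to intervention: school size, fidelity to implementation strategies, baseline organisational readiness, parent educational level" and parent country of birth. Earlier in that section, baseline characteristics "will be cross-tabulated for group 1 and 2 to check for balance" and to describe the study population.

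The only text that admits covariates to the primary analysis is in the Abstract (Methods), where the regressions are to be done "taking clustering and covariates into consideration where needed". A detailed SAP is promised before data analysis starts.

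On prognosis, the Background treats organisational readiness as a determinant of adoption that staff need in order to persist toward fidelity. From earlier evaluations it reports "difficulty to engage parents in low-income areas due to stressful everyday life and lack of knowledge and parenting skills". Table 1 lists socioeconomic and cultural factors and parents' engagement in schoolwork among the determinants, with workshop notes expecting poorer homework adherence in disadvantaged areas.

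On timing, Table 5 puts readiness in September 2021, and Randomisation and blinding places allocation after that baseline measurement. Parent demographics follow in October 2021 (cohort 1) and October 2022 (cohort 2).

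**The concern.** Thirty schools are randomised, so differences between schools make up a substantial part of the error in the arm comparison. Baseline variables that predict fidelity can remove some of that error at no recruitment cost. The article identifies such variables and collects them, but the only role it gives them is in exploratory moderator analyses. A moderator analysis asks whether the arm effect differs across levels of a variable; it does not sharpen the estimate of the overall effect.

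The covariate rule that does reach the primary models is conditional and has no stated criterion. A SAP written to match it could fix the covariates in advance or could let them depend on observed imbalance. School staff and the research team are not blinded to allocation, so a rule that leaves room for discretion is best closed before outcome data arrive. What is at stake is some power in a trial with little to spare once clustering is counted, and one avoidable choice in the primary result.

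**Working it through.** **1. The plan's own figure.** Under Sample size and power calculation, power "was calculated for the sample size of 400 consenting parents in each group". The responsiveness differences are 0.8, 1.6 and 3.2, and the article reports: "With an SD of 8, the power for the three scenarios is 0.29, 0.81 and 0.99 respectively for this outcome". For two independent means at two-sided 0.05 (assumed; the article states no alpha), SE = 8 × √(2/400) = 0.566. The ratios of difference to SE are 1.41, 2.83 and 5.66, and power = Φ(ratio − 1.96) = 0.293, 0.807 and 0.9999. These agree with the stated values, so the responsiveness calculation counts neither clustering nor covariates.

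**2. Responsiveness with clustering.** From the article: 30 schools, 1:1 allocation, 400 parents per arm, effect 1.6/8 = 0.2 SD. Assumed: 15 schools per arm, 400/15 = 26.7 parents per school, ICC 0.02 or 0.05, municipality in every model, and the share of variance the covariates explain between schools (Rb) and within schools (Rw).

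Var(arm effect) = (2/15) × [ICC(1 − Rb) + (1 − ICC)(1 − Rw)/26.7], in SD² units. Power comes from the noncentral t, with 27 df unadjusted (30 − 2 − 1) and 25 df adjusted (two more school-level df spent).

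At ICC 0.05 unadjusted: (2/15) × [0.05 + 0.95/26.7] = (2/15) × 0.0856 = 0.0114, SE 0.107, ratio 0.2/0.107 = 1.87, power 0.439.

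| Rb / Rw | Power, ICC 0.02 | Power, ICC 0.05 |
|---|---|---|
| unadjusted, 27 df | 0.601 | 0.439 |
| 0 / 0, 25 df | 0.599 | 0.436 |
| 5% / 1% | 0.609 | 0.449 |
| 10% / 2% | 0.620 | 0.461 |
| 20% / 2% | 0.636 | 0.486 |
| 40% / 5% | 0.681 | 0.549 |
| 60% / 10% | 0.738 | 0.636 |

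Weak covariates (second and third adjusted rows) add 0.01 to 0.02. Strong ones (last row) add 0.14 at ICC 0.02 and 0.20 at ICC 0.05. Useless ones cost 0.002 to 0.003. Spending one df instead of two changes the adjusted figures by at most 0.002.

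**3. Share of error between schools.** At ICC 0.05 the between-school term is 0.050 and the within-school term 0.95/26.7 = 0.0356, so 58% is between schools. At ICC 0.02 the terms are 0.020 and 0.98/26.7 = 0.0368, so 35% is.

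**4. Adherence.** The ordinal model behaves differently. A simulation used 400 per arm, no clustering, an assumed conditional log odds ratio of 0.4, one normal covariate and 250 replicates.

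| Latent R² | Unadjusted log OR | SE unadjusted | SE adjusted | Power unadjusted | Power adjusted |
|---|---|---|---|---|---|
| 0.03 | 0.39 | 0.128 | 0.128 | 0.89 | 0.87 |
| 0.10 | 0.38 | 0.127 | 0.129 | 0.85 | 0.91 |
| 0.20 | 0.36 | 0.127 | 0.130 | 0.80 | 0.89 |

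Adjustment does not lower the standard error. It targets a conditional odds ratio further from 1, and power may rise for that reason. Differences of about 0.02 are simulation noise: √(0.85 × 0.15/250) = 0.023.

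**The case against.** The strongest objection is that a covariate list is ordinary SAP content, and the article promises a SAP before analysis. That stands: the absence of a list is not the finding. What remains is what the article does state, namely a moderator role for its best available predictors and an unspecified conditional rule for primary adjustment.

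Several stronger readings are tempting but not supported:

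- A reader might infer that these variables are barred from the primary models. The Abstract allows covariates, and a factor listed as a moderator may also enter as a main effect.
- A reader might join the balance table to the conditional wording and infer that covariates will be chosen by observed imbalance. The article leaves this possible but never says it.
- School size might be read as a named driver of fidelity. It appears only in the moderator list. Non-Nordic origin is linked in the Background to diet and obesity; its link to fidelity is only through the broad socioeconomic and cultural determinant.
- All the variables might be taken as measured before allocation. Readiness is. Parent demographics are collected afterwards, and although allocation should not change education or birthplace, it could affect who consents and answers.
- Both models might be thought to lose precision. In the ordinal model that is the wrong term, as the simulation shows.

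It is also fair that no strength of association is given anywhere, so an honest range includes almost no gain.

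**Conclusion.** The point holds as a worthwhile improvement; it does not show a wrong analysis. The article gives its primary models no covariates, places readiness, parent education and country of birth among the moderators to explore, and leaves adjustment to an undefined condition. Fixing a short set in advance is nearly free and closes that discretion.

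The size of the gain is not established by the documents. Under the assumed ICC of 0.02 to 0.05, 26.7 parents per school and an effect of 0.2 SD, responsiveness power rises by about 0.01 to 0.02 with weak covariates and 0.14 to 0.20 with strong ones, with a loss of at most 0.003 if they explain nothing. It would go too far to say that between-school variance dominates the error: that is so at ICC 0.05 (58%) but not at 0.02 (35%). For adherence the possible benefit is power for a conditional effect, with no reduction in standard error.

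**What to change.** State in the analysis section and the SAP, before any outcome data are seen, that both primary models include municipality (the randomisation stratum), school mean baseline readiness, parent education and parent country of birth as fixed main effects, regardless of observed balance, with school as the clustering unit. Say which of the three readiness scores is used and how missing parent demographics are handled, bearing in mind that non-response arises after allocation.

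Report the model without the prognostic covariates as a sensitivity analysis. Keep the moderator interactions as separate exploratory models. Do not adjust for fidelity to implementation strategies: it shares the moderator list but is measured after randomisation and may be affected by arm. Replace the conditional wording in the Abstract with a reference to this fixed set.

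The cost is a sentence or two of text, one or two school-level degrees of freedom out of 27 and, for adherence, an odds ratio that must be reported as conditional, not marginal. No new data are needed.

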### Specific aims and hypothesis

The hypothesis is that the use of tailored implementation strategies with a focus on facilitation, monitoring, and feedback will lead to significantly better fidelity to the HSS intervention and to sustained effects on child and parent health outcomes. This study will be guided by the following research questions (question 1 has already been addressed):
What context-specific implementation determinants do stakeholders from municipalities in Sweden identify with regard to the implementation of the HSS program?Which of two bundles of tailored implementation strategies is most effective at improving fidelity, acceptability, appropriateness, feasibility, and organisational readiness to implement the HSS program?Does implementation of the HSS program at scale reduce social disparities in the proportion of children with overweight and obesity, and T2D risk among adults?What external implementation support will be needed to facilitate the sustainment of the program after the end of the study?

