### Eligibility of families, inclusion criteria

All children starting pre-school class (5–7 years of age) during the school year 2021/22 and 2022/23 and their parents/guardians are eligible for the study. The HSS program will be presented to parents as part of ordinary school routines, which means that all children and parents will take part in the program and be invited to participate in the study. At the first meeting in school with the class teacher, parents will receive oral and written information about the HSS and the IMPROVE study and a consent form. They will be informed that all families will be exposed to the HSS as part of school routines, but that participation in the IMPROVE study is voluntary and that no personal information or identities will be disclosed.

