### Randomisation and blinding

Within each municipality, schools will be randomised 1:1 to group 1 (Basic: bundle 1) or group 2 (Enhanced: bundle 1 + 2) using a computer-generated assignment by an independent statistician after baseline measurement has been conducted in September 2021. It is not possible to blind school staff and the research team to allocation, but parents and children will not get this information. The CONSORT flow diagram with the number of schools and children is shown in Fig. 2.

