#### Child height and weight

Child height and weight will be measured by the school nurse in pre-school class and again in year 2 including all children starting school in 2021 and 2022 (cohort 1 and 2) according to standard practice. We will use the extended international (IOTF) body mass index (kg/m^2^) cut-offs to define thinness, overweight and obesity [62]. The BMI z-score will be calculated according to a Swedish reference standard as described previously [29]. Weight and height data of all children that are routinely collected during health visits will also be obtained at the school level (de-identified, no consent needed) to be able to compare the weight status of study participants with all children at the same school.

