In order to answer the question of whether implementation of the HSS program at scale reduces social disparities in child weight status parent’s T2D risk we will do as follows. The secondary outcomes analysed will be the change in prevalence of child overweight and obesity, children’s sex and age-adjusted BMI and parents’ risk of T2D. Dichotome outcomes will be analysed with a logistic regression model and continous outcomes with linear or quantile regression models. We will use a method able to account for the within-school and within-person clustering such as mixed models or generalised estimation equations (GEE). Parent country of birth and child sex will be explored as moderators of child and parent outcomes in addition to intervention fidelity and other school-related factors mentioned above.

Effects of implementation strategies on primary and secondary outcomes within-group will be assessed yearly relative to baseline using repeated measures analyses. All analyses will be conducted on an intention-to-treat basis. Sensitivity analysis will be carried out for primary and secondary outcomes after imputing relevant missing data, if relevant.

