### WHO trial registration data set

**Table Taba:** 

Data category	Information
Primary registry and trial identifying number	ClinicalTrials.gov ID: NCT04984421
Date of registration in primary registry	July 30, 2021
Secondary identifying numbers	None
Source(s) of monetary or material support	Swedish Research Council for Health and Working Life and Welfare (FORTE)
Primary sponsor	Swedish Research Council for Health and Working Life and Welfare (FORTE)
Secondary sponsor(s)	NA
Contact for public queries	MSc, PhD [contact]
Contact for scientific queries	MSc, PhD, [name], Karolinska Institutet, Stockholm, Sweden
Public title	IMPROVE
Scientific title	IMplementation and evaluation of the school-based family support PRogram A Healthy School Start to promote child health and prevent OVErweight and obesity (IMPROVE) – study protocol for a cluster-randomized trial
Country of recruitment	Sweden
Health condition(s) or problem(s) studied	Unhealthy diet, low physical activity, overweight and obesity, type 2 diabetes
Implementation intervention	All schools receive the Heathy School Start intervention. Active: Implementation strategy bundle 1 + 2 (Enhanced) Comparator: Implementation strategy bundle 1 (Basic)
Key inclusion and exclusion criteria	Inclusion: Public schools in two municipalities in the Stockholm Region. All children in pre-school class 5–7 years in these schools Exclusion: None
Study type	Parallel group cluster randomised trial
Date of first enrolment of schools	August 2021
Recruitment status	Not started
Primary outcome(s)	Fidelity to intervention (adherence and responsiveness)
Key secondary outcomes	Acceptability, appropriateness, feasibility, organizational readiness, fidelity to implementation strategies, child diet, child BMI, child weight status, parent’s risk of T2D, parental feeding practices

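### Every school receives HSS, so the social-disparity question can be answered only for Enhanced versus Basic support; its moderator list omits parental education and includes post-randomisation fidelity

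*Protocol article*

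**What the plan says.** Under Specific aims and hypothesis, the third research question is: "Does implementation of the HSS program at scale reduce social disparities in the proportion of children with overweight and obesity", with adult type 2 diabetes (T2D) risk added. The section Data management and statistical analysis takes it up directly, opening a paragraph with "In order to answer the question of whether implementation of the HSS program at scale reduces social disparities". That paragraph names the outcomes (change in child overweight and obesity, standardised BMI, parents' T2D risk), logistic, linear or quantile regression, and mixed models or GEE for clustering. It ends with the effect modifiers: "Parent country of birth and child sex will be explored as moderators of child and parent outcomes in addition to intervention fidelity", followed by a reference back to other school-related factors.

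On exposure, the WHO trial registration data set states "All schools receive the Heathy School Start intervention", and the eligibility section tells parents that "all families will be exposed to the HSS as part of school routines". On allocation, the protocol states that "schools will be randomised 1:1 to group 1 (Basic: bundle 1) or group 2 (Enhanced: bundle 1 + 2".

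A separate list gives the candidate moderators of the primary outcome, fidelity: "school size, fidelity to implementation strategies, baseline organisational readiness, parent educational level and country of birth".

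**The concern.** The question is about an effect of HSS, but the only randomised contrast is between two levels of support for delivering HSS. With no unexposed group, a widening or narrowing of the social gap between first and last measurement mixes any HSS effect with whatever would have happened to that gap anyway. A report following this paragraph could claim that HSS reduced (or failed to reduce) disparities when the data cannot separate the two.

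Two features of the moderator list add to this. Parental education, one of the two social markers in the Background, is not named for child and parent outcomes. Intervention fidelity is named, although it is an outcome of the trial and not a baseline characteristic.

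**Working it through.** The protocol gives no figure for this question; its sample-size section covers only the adherence and responsiveness scores. The check is therefore a comparison of sections, plus one illustration with assumed inputs.

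**1. Which contrasts exist?**

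| Contrast | Available? | What it identifies |
|---|---|---|
| HSS versus no HSS | No: all schools and families are exposed | – |
| Enhanced versus Basic, overall or by social group | Yes, randomised by school | Effect of the added support, given HSS |
| Last versus first measurement under HSS | Yes, uncontrolled | HSS plus age and calendar trends |

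Only the first row would answer the question as worded.

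**2. How far can a gap move with no HSS effect?** For each social group, prevalence after = expit(logit(prevalence before) + *t*), where *t* is a background trend in log-odds. Assumed starting values are 30% (lower social group) and 15% (higher), a two-fold ratio; the Background cites a 2–3 fold difference. The logits are ln(0.30/0.70) = −0.847 and ln(0.15/0.85) = −1.735. The HSS effect is set to zero.

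| *t* lower / *t* higher | Lower after | Higher after | Gap (points, from unrounded values) |
|---|---|---|---|
| 0 / 0 | 30.0% | 15.0% | 15.0 |
| +0.1 / +0.3 | 32.1% | 19.2% | 12.9 |
| +0.2 / +0.2 | 34.4% | 17.7% | 16.6 |
| +0.3 / +0.1 | 36.6% | 16.3% | 20.3 |

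Starting instead from 30% and 12% (2.5-fold), the 18.0-point gap becomes 16.6, 20.1 and 23.6 in the same order of trends. The gap can shrink or grow with no program effect; even equal log-odds trends change it on the percentage-point scale.

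**3. Is parental education in the list?** The Background describes disparities by parental education and by non-Nordic origin. The Parent outcomes section collects both educational level and country of birth at baseline. The list for fidelity names both; the list for child and parent outcomes names country of birth and child sex. The reference back to school-related factors does not naturally carry education over: education is not a school-related factor, and country of birth, from the same earlier list, had to be named again.

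**4. When is fidelity measured?** Study design calls fidelity the primary dependent variable. Randomisation follows the September 2021 baseline. Table 5 dates fidelity to the HSS components to June 2022 (cohort 1) and June 2023 (cohort 2). Bundle 2 in Table 3 includes yearly audit and feedback on the fidelity score. Fidelity is thus downstream of allocation and a direct target of the Enhanced bundle.

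**5. Precision of the proposed interaction.** Take the planned 400 parents per arm, an even split by education (assumed), no clustering and full follow-up. In units of the outcome variance, the arm contrast has variance 1/400 + 1/400 = 0.005. The arm-by-education contrast has 4 × 1/200 = 0.020. The standard error is √(0.020/0.005) = 2 times as large, so these tests are exploratory.

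**The case against.** The best defence is that this is a hybrid type 3 trial. The second aim is worded as monitoring recipient outcomes, HSS was set against control in earlier trials, the moderators are only to be explored, and a detailed analysis plan is promised before analysis. All of that lowers the weight of the point. It does not remove it: the research question and the analysis paragraph both use causal wording about HSS, and no later plan can supply an unexposed arm.

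Country of birth is a genuine social marker, so the social dimension is incomplete and not absent. The reference back to earlier factors is loose enough that education may have been intended. That makes the education point minor on its own, but easy to settle.

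Four stronger readings are tempting and should not be taken.

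- A reader might infer that the trial can say nothing about disparities. It can describe the gap by country of birth over time and compare Enhanced with Basic; what it cannot do is attribute a change to HSS.
- A reader might infer that any rise in overweight with age would be read as a program effect. The question concerns a social gap, not overall prevalence, and the plan uses age-standardised BMI and age-specific cut-offs. What remains is differential age trend and calendar trend, for which the protocol gives no figure.
- A reader might infer that the plan fits a biased arm-by-fidelity interaction. The text specifies no such model. The supportable criticism is that a post-randomisation outcome is called a moderator.
- A reader might infer that the routine school-level weights could supply a historical control. They are described only for comparing participants with all children at the same school. They are de-identified, no parental education or FINDRISC is described for them, and access to earlier, unexposed year groups is not stated.

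**Conclusion.** The point holds for attribution. As worded, the third research question has no identifying contrast in this design, and the analysis paragraph should not be presented as answering it. This rests on the protocol's own statements about exposure and allocation and on no numerical assumption. The 12.9 to 20.3 point range is illustrative, and depends on the assumed prevalences and trends.

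The omission of parental education is the plain reading of the text, not a certain one. The fidelity point is about labelling: such an analysis can be informative about process, but it is not moderation of a randomised effect.

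This should be corrected, but it concerns secondary outcomes. The primary comparison of adherence and responsiveness between arms, and its power figures, are untouched.

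**What to change.** 1. Restate the third question as whether Enhanced rather than Basic support changes social differences in child weight status and parents' T2D risk. Describe any pre-post change in the gap under HSS as descriptive.
2. Name parental education and country of birth as the social-position variables. Test arm × education and arm × country of birth on follow-up BMI z-score, overweight/obesity and FINDRISC, adjusted for the first measurement and accounting for school clustering. Table 5 puts the first FINDRISC in October and the first weight in December, while randomisation follows the September 2021 baseline. The plan should therefore acknowledge that the adjustment variable may be measured after allocation.
3. Take intervention fidelity out of the moderator list for child and parent outcomes, and report analyses by fidelity as exploratory process or mediation associations. If the reference back to school-related factors was meant to include fidelity to implementation strategies, label that the same way.

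The cost is wording in the protocol and analysis plan. Education, country of birth and the outcomes are already collected. The downside is a more modest claim, with interaction tests of limited precision.
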